### Randomisation

When eligibility assessment was completed, participants were randomised to one of the two study arms using a computer-generated allocation sequence (https://www.randomizer.org) with separate sequence lists for each treatment centre. The participants were randomly assigned in a 1:1 ratio. Codes were used to ensure information confidentiality and participant anonymity. Moreover, the principal investigator, who had no access to the identity of the participants, performed the treatment allocation based on the codes. Participants were not blinded to the treatment condition.

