### Participants and procedures

Recruitment, treatment and data collection are conducted in seven cities in Sweden (Gävle, Falun, Karlstad, Uppsala, Uddevalla, Västerås and Växjö Additional file 1), beginning in 2015, with the last post-treatment measurement expected to be finalised in the spring of 2019. Adolescents (15–18 years of age) from the local child and adolescent psychiatric (CAP) outpatient units with a known diagnosis of ADHD have been informed about the study through flyers in waiting rooms, verbally by the clinical staff, or both. For those who have shown interest, more information has been provided at an extra meeting and the staff have evaluated the patients’ eligibility for the study (see below). Before final inclusion, participants and their parents provided written informed consent. Study participation is voluntary and can be interrupted by the participant at any time. Eligible patients have then been randomised to one of the two treatment conditions. Adolescent self-reports and parental ratings have been collected 2 weeks before the start of the treatment, during the treatment, and are continuously collected 2 weeks and 6 months after conclusion of the treatment. Pre- and post-treatment instruments are administered using an online platform to which only the research group has access and coded data is stored in a secure server. The participating parents are continuously reminded by the research team to complete the questionnaires. When both the adolescent and their parent have completed the last measurement, they will receive two cinema tickets. Initially, the plan was to continue the recruitment until at least 100 patients had completed treatment. In total, 184 patients have been randomised. Of these, 159 adolescents and 162 parents have completed baseline assessments and the last post-treatment evaluations are now continuously being collected (Fig. 1). Those who were randomised but never underwent a baseline assessment were considered external dropouts. Those who completed the baseline assessment, but did not complete the treatment, will be considered internal dropouts.

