### Eligibility criteria

To participate in the study the adolescents had to be 15–18 years old, be a patient at one of the designated CAP units and have a diagnosis of ADHD/ADD or ADHD-not otherwise specified according to ICD-10. The diagnosis is validated by using the section for ADHD in the Mini International Neuropsychiatric Interview for Children and Adolescents (MINI-KID) [30]. The assessment was performed by clinical psychologists who were trained in MINI-KID and who also assessed the participants’ eligibility for the inclusion and exclusion criteria. Adolescents were excluded if they showed symptoms of severe depression, suicidality, psychosis or bipolar disorder without a stable medication, a diagnosis of mental retardation, diagnosed organic brain injury, autism spectrum disorder or ongoing substance abuse. Ongoing pharmacological treatment had to be stable and the participants were asked not to change medication during the period of treatment. In addition, the clinical staff were also informed not to change medication or medication dose during the treatment period. Nevertheless, patients will not be excluded if their medication were changed during the treatment period; instead, any changes in medication will be adjusted for in the analyses. The participants were requested not to participate in any other psychological treatment during the treatment period and the parents were requested not to participate in any parent educational programme during this period. The treatment took place at the adolescents’ CAP units and any deterioration of symptoms during the treatment are handled by the units. Any negative reaction could be discussed with the supervisor. Since the treatment is given as part of the regular health care, the patients are covered by the patient injury insurance.

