### Statistical methods

#### Statistical analysis plan

The treatments were finalised during 2018 while post-treatment ratings are currently being collected. Analysis of the data will start in the summer of 2019. The statistical analysis will be conducted on all participants who completed the pre- treatment (baseline) questionnaires (*n* = 159 adolescents and *n* = 162 parents). Missing post-baseline data for any of the participants because of the absence of any session or dropout will be handled by multiple imputations using last mean carried forward (LMCF) [47]. A sensitivity analysis will be performed for those who completed the treatments (e.g., attended at least two thirds of the sessions) without using LMCF. Primary and secondary outcome variables will be analysed with repeated measurements in general linear models using the baseline value for respective outcome as a covariate. The primary analysis will be aimed at investigating differences between the two treatment groups in reduction in ADHD symptoms and functional impairment, and increase in mindfulness and quality of life, directly and 6 months post-treatment. Secondary analyses will be aimed at investigating the group treatment effects on reported symptoms of comorbid psychopathology and health-related status. Moreover, the two treatment groups will be compared for treatment acceptability. As separate analyses, we intend to explore any difference in outcome measures based on subgroups of clinical relevance (e.g., subtype of ADHD and symptoms of other psychopathology). We also plan to validate and investigate the psychometric properties of the newly developed questionnaire, IAS, which was constructed to assess the impact of ADHD symptoms on the adolescents’ wellbeing during the treatment intervention. Guidelines for the specific rating scale will be used in the choice of imputation of missing data within the scales. If no guidelines are available, an imputation of the mean of the subscale for that specific participant will be used when less than 20% of the items are missing.

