### Sample size

Sample size was calculated using G*Power software version 3.1.9.3 with a power of 0.80 and α = 0.05 (two-tailed). Based on the results from previous studies on CBT/DBT treatment for adults and adolescents with ADHD [15, 21] we expect a reduction on the ASRS-A of about seven points (range is 0–72). A greater reduction of ADHD symptoms in the SSTG of seven points (SD = 12) on the ASRS-A and a greater reduction of four points (SD = 7) on functional impairment as measured by the CSDS would result in an effect size of 0.57 and a sample size of approximately 50 participants per group. Based on pre- and post-treatment measurements using the SDQ from the pilot study, at least 17 adolescents are needed to obtain a reduction of symptoms and 69 adolescents for a reduction of self-rated impairments using the paired sample t-test. Based on these power calculations and what was deemed feasible in the clinical settings, a study population of ≥100 was targeted.

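### Allocation used a separate list for each of seven centres, but the stated analysis model has no centre term

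*Protocol article*

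**What the plan says.** **Allocation.** The Randomisation section of the protocol article describes a computer-generated sequence "with separate sequence lists for each treatment centre" and states: "The participants were randomly assigned in a 1:1 ratio". It mentions neither blocks nor any other device to keep the arms balanced within a list.

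**Centres.** Participants and procedures states: "Recruitment, treatment and data collection are conducted in seven cities in Sweden".

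**Model.** The Statistical analysis plan section assigns primary and secondary outcomes to "repeated measurements in general linear models using the baseline value for respective outcome as a covariate". This is the only covariate named there. The analysis set is everyone with baseline questionnaires: 159 adolescents and 162 parents, out of 184 randomised.

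**Other adjustment.** Eligibility criteria adds that "any changes in medication will be adjusted for in the analyses". No section puts centre, site or list into any analysis.

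**The concern.** Separate lists per centre make centre a stratification factor, and an analysis normally includes the factors by which allocation was stratified. There are two cases.

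- **Lists balanced within centre.** Centre differences cancel from the treatment contrast. A model without centre still counts them as residual noise, so the reported standard error is larger than the true one and the test is conservative.
- **Lists not balanced within centre.** Chance imbalance lets centre differences into the contrast. The standard error describes that noise correctly, but the noise could have been removed.

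Some variation between centres is plausible, because treatment was given at each adolescent's own unit by local pairs of therapists. At stake is precision on every primary and secondary outcome. There is also a question of discipline: a centre term chosen after the results are known would be a discretionary choice across many outcomes.

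**Working it through.** **1. The plan's own figure.** Inputs from Sample size: effect size 0.57, power 0.80, two-sided α 0.05.

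n per group = 2(1.960 + 0.842)² / 0.57² = 15.70 / 0.325 = 48.3, so 49 by the normal approximation and 50 by the exact t-test. The stated figure of about 50 is reproduced. It contains no centre term, so nothing here changes it.

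**2. Closed form, perfectly balanced lists.** Let ρ be the share of residual variance (after the baseline covariate) that lies between centres. The documents give no value, so 5% and 10% are assumptions.

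- Ratio of reported to true SE = 1/√(1 − ρ): 1/√0.95 = 1.026 and 1/√0.90 = 1.054.
- Actual size of a nominal 5% test = 2[1 − Φ(1.96/√(1 − ρ))]: 0.044 and 0.039.
- Equivalent loss in reported information, ρ × 159: 8 and 16 participants.

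**3. Simulation.** ANCOVA on a single post-treatment value, N = 159, seven equal centres, total residual variance fixed at 1, and lists either in blocks of four or unblocked. There were 6,000 replicates for size and 3,000 for power. Power is at an effect size of 0.45, chosen because it puts power near 0.80. Each cell gives the result without centre / with centre.

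| Centre share | Size, blocked | Power, blocked | Size, unblocked | Power, unblocked |
|---|---|---|---|---|
| 0 | 0.050 / 0.051 | 0.792 / 0.793 | 0.049 / 0.047 | 0.787 / 0.778 |
| 0.02 | 0.050 / 0.052 | 0.795 / 0.798 | 0.054 / 0.054 | 0.810 / 0.801 |
| 0.05 | 0.049 / 0.055 | 0.810 / 0.823 | 0.050 / 0.053 | 0.805 / 0.800 |
| 0.10 | 0.044 / 0.053 | 0.816 / 0.839 | 0.051 / 0.048 | 0.809 / 0.822 |
| 0.20 | 0.033 / 0.051 | 0.845 / 0.886 | 0.050 / 0.048 | 0.813 / 0.873 |

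Monte Carlo standard errors are about √(0.05 × 0.95/6000) = 0.003 for size and √(0.8 × 0.2/3000) = 0.007 for power.

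A further run of 6,000 replicates also recorded the mean reported SE. With blocks of four, leaving centre out raised it by 2.1% at a 5% share and by 4.6% at a 10% share. Size was 0.043 without centre against 0.048 with it (5% share), and 0.045 against 0.053 (10% share). Power was 0.815 against 0.827, and 0.819 against 0.841. For unblocked lists, power was 0.812 against 0.817, and 0.805 against 0.831, with size about 0.05 either way.

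**4. Reading the results.**
- Blocked lists, 5–10% share: size without centre is 0.043–0.049, and the power loss is 1.2–2.4 points. The closed form is a little more pessimistic because blocks of four do not balance every centre exactly.
- Unblocked lists: size without centre stays at 0.049–0.054 for every share. The effect on power runs from nothing detectable at 5% to 1–3 points at 10%.

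**The case against.** **The covariate list may not be complete.** The statistical section names the baseline value but does not exclude other terms. The medication adjustment, promised in another section, shows that its list is not exhaustive. A reader might infer that the model adjusts for the baseline value alone, or that the stratification has been deliberately ignored. The article supports neither. What stands is narrower: it names a model, a covariate and one further adjustment, and the randomisation factor is not among them.

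**The harm depends on an unstated condition.** A reader might infer that the standard errors are necessarily wrong. That holds only if the lists were balanced within centre. Unblocked lists behave like simple randomisation, and the test then keeps its size. This objection stands in full.

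**Centre differences are not documented.** A reader might take it as given that case mix and usual care differ between centres. The article reports no such difference. It describes common eligibility criteria, manualised treatments, yearly meetings and supervision. The centre share is therefore an assumption.

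**The trial has power to spare.** At the planned effect size of 0.57, normal-approximation power with 159 is Φ(0.57√(79.5/2) − 1.96) = Φ(1.63) = 0.95. With 16 fewer, it is Φ(0.57√(71.5/2) − 1.96) = Φ(1.45) = 0.93. This is a fair measure of how little is lost at the planned effect.

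**Therapy groups.** It is tempting to fold clustering by therapy group into this point. That is a separate matter, and it tends to make tests too liberal rather than conservative. The figures here do not bear on it, and a centre term does not resolve it.

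**Conclusion.** The point holds as a modest one. Centre defines the allocation lists, and no analysis described in the article includes it.

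With lists balanced within centre and a centre share of 5–10%, the reported standard error is roughly 2–5% too large. The nominal 5% test then runs at about 4–5%, and about 1–2 points of power are lost at N = 159 for an effect size of 0.45. With unblocked lists the test is valid as it stands, and only some precision may be lost. Because the analysis set is 159 of 184 randomised, even blocked lists may have lost some of their balance, which would put the trial between the two cases.

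Both the centre share and the balance of the lists are assumptions. Nothing here points to false positives. The case for acting is that the change is cheap and is best made before results are seen.

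**What to change.** Add centre as a fixed effect with seven levels to every primary and secondary model, beside the baseline value of the outcome. Record this before the analysis starts, which the article sets for summer 2019. State at the same time whether the centre lists were blocked, since that decides which of the two cases applies.

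The cost is six degrees of freedom out of about 150, and no new data. If centre explains little or nothing and the lists were unblocked, the simulation at N = 159 puts the price at up to about one point of power (0.787 without centre, 0.778 with it, at a zero share). That is close to simulation error.

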### Trial arms

#### Structured skills training group (SSTG)

The treatment is an age-adjusted version of a manualised DBT-based group programme originally developed in Germany for adults with ADHD [19, 31] and later translated and evaluated in a Swedish population [22, 32]. The SSTG consists of 14-weekly 2-h sessions. Each session has its own theme (Table 1), including discussions and exercises. The themes are presented to the participants in a workbook and through a PowerPoint presentation. Themes specific for DBT, such as mindfulness, acceptance and behavioural analysis, are continuously practised during the treatment sessions. Each group was led by two therapists, of which at least one was trained in DBT. All of the therapists are educated in the treatment and they discussed the manual in yearly meetings. A clinical psychologist, trained in both CBT and DBT, offered the therapists continuous supervision throughout the study. In addition, the therapists were instructed to video record the group sessions to enable assessment of manual adherence.

**Table 1 Tab1:** Description of the themes and content of the structured skills training group

Session	Themes
1.	*Introduction:* Introduction and overview of the treatment, psychoeducation about ADHD, strengths, and difficulties with ADHD and introduction of the main themes of treatment. Define goals. Give a home assignment, which is a central part of all sessions.
2.	*Neurobiology and mindfulness I:* Neurobiology of ADHD, emphasising difficulties in executive functions and the possibility to improve functions through practice, e.g. mindfulness training. Introducing mindfulness. Thereafter, mindfulness training is included in all sessions.
3.	*Homework and mindfulness II:* The purpose and importance of homework as a part of the treatment are emphasised. Participants receive tips for how to get the home assignments done.
4.	*Acceptance and mindfulness III*: The balance between acceptance and change is discussed. The concept of “wise mind” and the integration of the emotional mind and the reasonable mind is introduced.
5.	*Chaos and control:* Difficulties in organization and planning are highlighted and strategies with the aim to increase control are introduced.
6	*Emotions:* Education in emotion theory (primary emotions, connection between emotions, thoughts, behaviours, signals and communicatory aspects of emotions, emotions and ADHD). Practice in identifying, observing, and describing emotional signals to regulate and cope with emotions.
7–8.	*Behavioural analysis:* Participants are introduced to behavioural analysis (preceding events/internal and external “triggers”, behavioural responses, and consequences). Strategies to find alternative behaviours are introduced and practiced. Behavioural analysis is applied on own examples and thereafter used throughout treatment.
9.	*Medication, mental illness, and how to increase wellbeing:* Information and discussion about pharmacological treatment for ADHD, documented effects as well as side effects. Symptoms of depression and other emotional problems are discussed, also focusing on treatment, preventive strategies, and emotional regulation.
10.	*Impulsivity, risk behaviour, and addiction:* Symptoms of addiction and other forms of risky behaviours are discussed. Practice in identifying, describing, and regulating impulsive behaviours using mindfulness and behaviour analysis as strategies.
11.	*Stress:* Physiological reactions of stress and the relation between stress and performance are covered. Exercises in identifying and learning about own personal stress are performed. Strategies for stress management are taught.
12–13.	*Self-esteem and relationships:* Differences between self-esteem, self-confidence, and self-respect are clarified, including the impact of ADHD on these areas. Social skills are taught and practiced.
14.	*Retrospect and outlook:* The participants summarize their experience of the group treatment, identify achieved, as well as remaining goals and plan for maintaining progress and how to manage future problems.

A clinical child and adolescent psychologist, trained in both CBT and DBT, adjusted the manual for adolescents based on her clinical experience as well as from the results of the pilot study. The publisher gave us permission to continue to improve the manual for the age group. Further adaptations were discussed and revised in a reference group consisting of five psychologists and one social worker (two were trained DBT therapists and four CBT therapists), all working clinically in child and adolescent psychiatry. The following adaptations were implemented: The language was simplified and examples were adapted to the current age group; some theoretical sections were shortened and clarified; more practical exercises were included; and more examples of tools and skills were presented. Moreover, the number of homework assignments was decreased and no additional literature was recommended. One session was moved to an earlier stage in the programme (the session about emotions was now presented before the session about behavioural analysis) and the time spent on relational skills was increased with additional theory and practice. To make this feasible within the time frame of 14 sessions, the sessions about impulsivity and addiction were merged into one session. Major adaptations were done before the study start and some minor additions were introduced after the first round of treatment to further simplify and clarify the material. After the adaptations were consummated, the study supervisor reviewed the manual to ensure that the original method was preserved. All essential elements were kept.

### Outcome measures

#### Primary outcomes

##### Adult ADHD self-report scale for adolescents (ASRS-A)

ADHD symptoms are assessed using parental and self-ratings on the ASRS-A [33, 34] at pre- (baseline measurement) and post-treatment. Self-ratings were also conducted half-way through the SSTG. The ASRS-A is a modified version of the adult ADHD self-report scale. The instrument has shown promising psychometric properties in clinical populations [34]. The questionnaire contains 18 items corresponding to the diagnostic criteria of ADHD in accordance with the diagnostic and statistical manual of mental disorders, fourth edition (DSM-IV).

##### Impact of ADHD symptoms (IAS)

A six-item questionnaire was constructed for this study to repeatedly assess the impact of ADHD symptoms on the adolescents’ wellbeing. The questionnaire is completed by the adolescents both at pre- and post-treatment but also after each of the sessions. The adolescent responds to the extent their wellbeing has been affected by behaviours and symptoms (e.g., difficulties in regulating emotions and starting/completing assignments on time) related to ADHD during the past week. Each item is answered on a scale from 0 (“Not at all”) to 10 (“Very much”), with higher scores indicating greater impact of the ADHD symptoms on wellbeing. The scale will be validated within the study.

##### Child Sheehan disability scale (CSDS)

Adaptive functioning is measured using the CSDS [35] to assess how much the symptoms interfere with daily functioning (three items for adolescent self-ratings and five for parental ratings). The scale, which has shown good validity in a clinical sample of children and adolescents with psychiatric disorders [35], is a modified version of the Sheehan Disability Scale for adults [36, 37]. The questionnaire is answered before and after treatment by the adolescents and their parents. Self-ratings were also conducted half-way through the SSTG.

##### Global quality of life scale (GQL)

Perceived quality of life is measured with the GQL scale [38], which is a one-item question with a visual analogue scale (VAS). The adolescents answering the question, “How is your life right now?”. The original scale consists of a 10-cm line. However, in the present study measurements were presented in an electronic format in which the 10-cm layout was not possible. Thus, instead we used fixed values ranging from 0 (“The worst imaginable life situation”) to 10 (“The best imaginable life situation”). The GQL is completed by the adolescents before and after treatment as well as after every session. The psychometric properties of the GQL have shown to be acceptable [38].

